### Study methods

Participants will undergo standard pre-operative, anaesthetic, surgical and post-operative care according to existing institutional protocols. Decisions about the prevention or treatment of excessive bleeding during or after surgery will be guided by clinician judgement and routine laboratory investigations (such as measurement of heparin level) in accordance with our routine institutional practice. These decisions will not be influenced by study participation although clinicians will be asked to record the indication for each pro-haemostatic treatment during intervals A, B and C, as described above. Blood samples will be taken from existing vascular lines that are inserted as part of standard clinical care without the need for additional venepunctures.

In order to enable laboratory quality control and assay validation purposes, blood samples not used in the initial analyses will be stored at −80 °C for the duration of the study. Specimens that are left over upon completion of the study have the potential of being used for future research relevant to cardiac surgery. Therefore, participants or their parent/guardian are asked to give their permission for samples to be retained after the end of the study for use in other ethically approved research. The samples of participants who do not consent to this option will be destroyed at the end of this study in accordance with the Human Tissue Authority’s Code of Practice. The responsibility for custodianship of samples retained beyond the end of this study will lie with the Chief investigator.

Data collection will include the following elements: A log of all children having cardiac surgery A log of patients assessed against the eligibility criteria and, if ineligible, reasons for ineligibility. A log of potential participants or parents/guardians approached for the study (including the date when they are given the Patient Information Leaflet). Consent and baseline information, including demographic characteristics, clinical history, planned procedure. Data characterising the participant’s hospital stay Operative details Clinical observations and routinely collected laboratory test results Post-operative care Post-operative complicationsBlood clotting abnormality test results collected as part of the study will be obtained from the ROTEM device hard-drive, Multiplate device hard-drive, ETP device hard-drive, and for other tests, from the Bristol University Hospitals NHS Foundation Trust (UHBristol) electronic laboratory database. Data describing red blood cell, platelet and fresh frozen plasma transfusions will be obtained from the UHBristol blood bank electronic laboratory database. Data describing all other pro-haemostatic treatments.

A large amount of data will be available from routine sources such as medical records and intra/post-operative care charts. Study data will be recorded on a study CRF before transfer to a custom made electronic database held on a secure server. Study-specific CRFs will be used as required.

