### Primary outcomes

The primary outcome is clinical concern about bleeding. This outcome will be determined for the following time intervals:

Interval A: The period between sample 1 and sample 2

Interval B: The period between sample 2 and chest drain insertion.

Interval C: The first 12 h after chest drain insertion.

Clinical concern about bleeding is defined as:High blood loss. Chest drain volume of either >5 ml/Kg/hr in any 1 h interval or >3 ml/Kg/hr for 3 consecutive hours (Hazinski guidelines [7]) in interval C.ORAny non-routine pro-haemostatic treatment given in response to bleeding by the clinical team. This is defined as any of the following: protamine given after initial heparin reversal; fresh frozen plasma (FFP); cryoprecipitate; platelet concentrates; any anti-fibrinolytic drug; activated recombinant factor VII (rFVIIa); fibrin sealant or fibrinogen concentrate.

The composite endpoint is necessary because of two important constraints:Blood loss is readily quantified after chest drain insertion by measuring drain volume. However, in intervals A and B (before chest drain insertion), measurement of blood loss is not feasible.Non-routine pro-haemostatic therapies are usually given soon after the start of abnormal bleeding and, if effective, prevent further bleeding. Measuring only ‘high blood loss’ would result in the primary endpoint of excessive bleeding not being identified in these instances.

There are two other circumstances in which clinicians administer pro-haemostatic therapies during or after cardiac surgery in children:As part of our standard institutional protocols for all children in the study population. These are termed ‘routine’ pro-haemostatic therapies and include interventions such as cryoprecipitate infusion and the administration of protamine to reverse the effects of heparin at the end of surgery.In response to a perceived risk of excessive bleeding but before excessive bleeding starts. These are termed ‘non-routine prophylactic’ pro-haemostatic therapies and are usually given during interval B.

Clinicians will be asked to classify all pro-haemostatic treatments in the study intervals A-C into one of three categories i) ‘routine’, ii) ‘non-routine in response to bleeding’; or ‘non-routine prophylactic’ on the study CRFs. The ‘routine’ and ‘non-routine prophylactic’ pro-haemostatic treatments will not be considered part of the primary outcome.

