### Laboratory testing

Each blood sample will undergo parallel testing by:Thromboelastometry (ROTEM, Tem Innovations GmbH). Four different tests will be performed on this platform (INTEM, EXTEM, FIBTEM and HEPTEM tests using manufacturer's standard reagents). Each test will yield eight parameters; i) clot time (CT), ii) clot formation time (CFT), iii) alpha angle, iv) maximum clot firmness (MCF), v-vii) amplitude at 10, 20 and 30 min after CT and viii) lysis index at 30 min after CT.Reference laboratory tests. These tests will provide 10 measurements on each sample;Prothrombin time and activated partial thromboplastin timeFibrinogen activity (Clauss assay)Anti-Xa assay (heparin activity)Endogenous thrombin potential ((ETP); thrombin generation assay in plasma)Platelet countPlatelet function testing by whole blood electrical impedance aggregometry (Multiplate, Roche Diagnostics) with the Adenosine diphosphate (ADP-test), Thrombin Receptor Activating Peptide (TRAP-test) and Collagen (COLL-test) standard manufacturer's reagents. The platelet function test results will be expressed as area under curve, lag time and amplitude.

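### Heparin level can prompt the protamine that counts as a primary outcome event, so heparin-related tests may appear to predict bleeding when they partly predict treatment

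*Protocol article*

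**What the plan says.** Four parts of the protocol article bear on this.

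- **Primary outcomes.** A child is an event through high drain loss in interval C, or through any non-routine pro-haemostatic treatment given in response to bleeding. The qualifying list opens with "protamine given after initial heparin reversal; fresh frozen plasma (FFP); cryoprecipitate; platelet concentrates; any anti-fibrinolytic drug". The reason given for a composite is that "in intervals A and B (before chest drain insertion), measurement of blood loss is not feasible", so treatment is the only limb in those two intervals.
- **Primary outcomes, classification.** "Clinicians will be asked to classify all pro-haemostatic treatments in the study intervals A-C into one of three categories": routine, non-routine in response to bleeding, or non-routine prophylactic. The first and third kinds of "pro-haemostatic treatments will not be considered part of the primary outcome". Extra protamine to cover re-infused pump blood is also left out.
- **Study methods.** Treatment decisions are "guided by clinician judgement and routine laboratory investigations (such as measurement of heparin level) in accordance with our routine institutional practice". The next sentence adds that study participation will not influence them.
- **Laboratory testing and Statistical analyses.** Anti-Xa heparin activity is one of the reference tests. Under objective 2 each TEM and reference result is related to clinical concern about bleeding by logistic regression, and ROC analyses look for optimal cut-offs. Residual heparin, meaning raised APTT and raised anti-Xa with the other reference tests normal, is the article's own example of a diagnostic class to be related to the outcome.

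**The concern.** A predictor should be judged against an outcome that it does not help to bring about. Here heparin level is named as a guide to treatment, a treatment aimed at heparin counts as an event, and heparin activity is then assessed for how well it predicts that event.

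Take two children who ooze to the same degree. The one with a high heparin level is given more protamine, truthfully recorded as a response to bleeding, and becomes an event. The other is watched and, if drain loss stays low, is a non-event. The data then show heparin activity predicting bleeding although the bleeding was equal.

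The stated aim is better prediction of excessive bleeding, and the results are meant to inform future randomised trials. An association or cut-off for residual heparin that partly reflects prescribing habit would carry that habit into those trials as if it were a property of the test.

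**Working it through.** **1. Timing.** Sample 2 is taken after bypass has stopped and heparin has been reversed, and it closes interval A. A result reflecting residual heparin at that point cannot have prompted treatment in interval A. The path therefore runs mainly from sample 2 predictors to treatment in intervals B and C. In B treatment is the only limb; in C drain loss is also available.

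**2. Safeguards.** Treatment prompted by a result in a child who is not bleeding should be coded prophylactic and drop out, as should pump-blood protamine. What remains is treatment of a child who is bleeding, where the result tips the decision. The coding is done by clinicians whose decisions, by the article's own account, routine results help to guide.

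**3. Planned analysis.** The only bias that Statistical analyses addresses is optimism, through cross-validation or bootstrapping. Resampling does not help here, because the same link between predictor and outcome is present in every resample.

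**4. The plan's own figure.** Inputs from Sample size calculation: 200 children, 50% outcome rate, 30% with an abnormality, relative risk 1.5. Two-sided alpha of 0.05 is assumed, since none is stated.

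- Rate with a normal result: 0.5 / (0.7 + 0.3 × 1.5) = 0.5 / 1.15 = 0.435. Rate with an abnormal result: 1.5 × 0.4348 = 0.652.
- With 60 against 140 children and a continuity-corrected normal approximation, power is 76.7%, which matches the stated 77%.

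So the figures are sound. The point concerns what the outcome measures.

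**5. Illustration of size.** Suppose a test has no relation to bleeding. Let b be the outcome rate without result-prompted treatment, and q the share of otherwise event-free abnormal children who are treated because of the result and coded as events. Then

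apparent relative risk = [b + q(1 − b)] / b = 1 + q(1 − b)/b.

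| q | b = 50% | b = 43.5% |
|---|---|---|
| 10% | 1 + 0.1 × 1 = 1.10 | 1 + 0.1 × 0.5652/0.4348 = 1.13 |
| 20% | 1 + 0.2 × 1 = 1.20 | 1 + 0.2 × 0.5652/0.4348 = 1.26 |

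To reach the planned 1.5 with no true association, q would have to be 50% at b = 50%, or (0.6522 − 0.4348)/0.5652 = 38% at b = 43.5%.

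Neither q nor the frequency of residual heparin is in the document. Because only children who are bleeding can properly be converted into events, q cannot exceed the share of otherwise event-free abnormal children who bleed at all.

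**The case against.** The composite is a reasoned choice. The article explains why blood loss alone would miss bleeding that treatment has stopped, and it openly names the outcome clinical concern about bleeding. It also excludes the treatments most likely to be driven by results. Sensitivity analyses often sit in an analysis plan, which is not shown here. All of this stands, and it confines the point to a narrow path. It does not remove the path, because the outcome definition and the statement on what guides treatment are both fixed in this article. The assurance about study participation does not answer it either, since the influence comes from routine results.

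A reader might infer more than the document supports:

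- **That all reference tests drive treatment.** Only heparin level is named, and the article does not say that the routine measurement is the anti-Xa assay. Extending the point to PT, APTT, fibrinogen and platelet count is possible but not stated.
- **That clinicians saw the study results.** The article says that device results come from the device hard-drives "and for other tests, from the Bristol University Hospitals NHS Foundation Trust (UHBristol) electronic laboratory database". That describes where data are extracted. It does not say who could see the results, or when.
- **That the comparison is tilted against TEM.** TEM is not named among the routine guides, but the wording is illustrative and does not exclude it. Abbreviations describes HEPTEM as reflecting heparin activity, so any inflation can reach TEM tests too. Statistical analyses describes models for individual results and no formal contrast of TEM with reference tests.
- **That a test must also predict drain loss to count.** Effective treatment lowers drain loss, so a true predictor could fail that condition.

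**Conclusion.** The concern holds for heparin-related predictors, mainly at sample 2 and for intervals B and C. Followed as written, the plan can overstate how well anti-Xa and the residual-heparin class predict bleeding, and can shift their ROC cut-offs towards the level at which clinicians already treat. The direction follows from the text; the size does not. The relative risks of 1.20 to 1.26 rest on an assumed 20% share and on baseline rates of 50% and 43.5%. They show only that a modest share would matter against a planned relative risk of 1.5.

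One inconsistency widens the path if left alone. The Abstract defines the treatment limb by perceived high risk of bleeding, which Primary outcomes excludes. The two must be reconciled.

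**What to change.** Before database lock, specify two additions for objective 2:

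1. Repeat the models and ROC analyses for anti-Xa, APTT, INTEM, HEPTEM and the residual-heparin class with protamine removed from the treatment component.
2. Repeat all objective 2 models with measured high blood loss in interval C as a supporting outcome.

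Report both beside the composite. Describe a heparin-related test as predicting bleeding, as distinct from predicting treatment, only with these results shown. Drain loss should inform the reading and should not act as a veto. If the analysis plan already contains these analyses, the point is met.

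The cost is extra model runs. Drain volume, extra protamine and the indication for each treatment are already to be collected, and no interim analysis is planned. The drawback is fewer events and wider intervals. Each repeat can also err the other way: heparin-related bleeding stopped by protamine alone becomes a non-event in the first, and bleeding stopped by any treatment can be missed in the second.

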### Statistical analyses

In order to address objective 1 (describing the prevalence of the different types of blood clotting abnormality before and after cardiac surgery) the following analyses will be undertaken:The distributions of the measurements from each reference laboratory test will be characterised separately for the two sample time-points.Principal component, latent class or similar analyses will be selected depending on the nature of the distributions and will be used to define and describe blood clotting abnormalities on the basis of the reference laboratory test results.The proportions of participants with different blood clotting abnormalities based on the classification determined in b) and with no blood clotting abnormality will be described with 95 % confidence intervals.

Logistic regression models will be fitted to estimate extent to which the individual results of the TEM and reference laboratory test results at each time point predict clinical concern about bleeding (objective 2a). Receiver operator characteristic (ROC) analyses will be performed to identify optimal cut-off criteria for predicting clinical concern about bleeding using separate analyses for each category of blood clotting abnormalities. The most prevalent clusters of abnormal reference laboratory test results (identified in objective 1) will be represented as semantic diagnostic terms representing different possible blood clotting abnormalities (e.g. increased APTT and increased anti-Xa heparin activity, but normal other reference laboratory tests indicates "residual heparin") and associations between these terms and clinical concern about bleeding will be investigated using logistic regression models (objective 2b).

We will estimate the diagnostic accuracy of TEM test results for the different types of blood clotting abnormality defined by the results of the reference laboratory tests (objective 3) by calculating the sensitivity and specificity, likelihood ratios and positive and negative predictive values for different estimates of the prevalence of blood clotting abnormality.

The agreement between the recommended treatments resulting from the reference tests and the TEM test results will be assessed using Kappa statistics (objective 4). The proportion of participants correctly identified by diagnostic models using either TEM or reference test results will be subject to ‘optimism’ bias. Ideally, this would be addressed by validating models on ‘new’ data that is not used for developing the models (‘train-and-test’ validation). Since the sample size available for this study is not large enough to permit this, we will consider alternative methods such as cross-validation and boot-strapping.

Analyses relating to objectives 1, 2 and 3 above may additionally be stratified by age group. The primary analysis will take place when all data have been collected, samples analysed and the database is locked. No interim analysis is planned.

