## Methods and design

### Aims and objectives

The overall aim of the study is to evaluate whether TEM testing for blood clotting abnormalities in children before or after cardiac surgery will improve prediction of excessive bleeding after cardiac surgery.

This may confer direct clinical and economic benefits in two ways; 1) test results may improve selection of the best treatments for children with blood clotting abnormalities to prevent or stop excessive bleeding, and, b) test results may prevent the use of unnecessary treatments in children who do not have blood clotting abnormalities and are at low risk of excessive bleeding.

The study objectives are as follows:To describe the prevalence of the different types of blood clotting abnormality in children before and after cardiac surgery.To estimate the extent to which the TEM and reference laboratory test results predict (a) clinical concern about bleeding after cardiac surgery and (b) different types of blood clotting abnormality and clinical concern about bleeding after cardiac surgery.To estimate the diagnostic accuracy of TEM test results vs. reference laboratory tests for the different types of blood clotting abnormality identified (a) before and (b) after cardiac surgery.To investigate the agreement between the treatment recommended by the results of the reference tests and the treatment recommended by the TEM test results(see Figure 1 for study schema)

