### Sample size calculation

The study size is 200 participants with blood samples taken. In estimating the power of the study and precision of the estimates, we have assumed that the rate of the primary outcome is 50 % in this population. Additionally, we have considered two alternative estimates of prevalence of blood clotting abnormalities (30 % and 5 %) in the study population:

**Objective 1** (describing the prevalence of different blood clotting abnormalities in the population): a sample size of 200 participants will allow a prevalence of 30 % to be estimated with a 95 % confidence interval of +/− 7 % (23.7 %, 36.9 %) and a prevalence of 5 % to be estimated with a 95 % confidence interval of +/− 4 % (2.4 %, 9.0 %).

**Objective 2** (estimating the extent to which TEM and reference laboratory test results predict clinical concern about bleeding): the power to estimate a relative risk of a given magnitude is dependent on the prevalence of the blood clotting abnormalities and increases with increasing prevalence. The study will have a minimum of 77 % power to estimate a relative risk of 1.5, given a rate of blood clotting abnormalities of >30 % in the population and >80 % power to estimate a relative risk of 2, given a rate of blood clotting abnormalities of between 4 % and 5 %.

**Objective 3** (estimating diagnostic accuracy of TEM test results vs. reference test results): a sample size of 200 participants will allow the sensitivity and specificity of each TEM test result to identify defined blood clotting abnormalities with a prevalence of 30 % to be estimated with a 95 % confidence interval of +/− 10 % (79.5 %, 96.2 %) for a sensitivity of 90 % increasing to +/−13 % (46.5 %, 72.4 %) for a sensitivity of 60 %. The specificity will be estimated with a 95 % confidence interval of +/−6 % (83.8 %, 94.4 %) for a specificity of 90 % increasing to +/−9 % (51.4 %, 68.2 %) for a specificity of 60 %. For a prevalence of 5 %, the 95 % confidence intervals are +/− 35 % (55.5 %, 100 %) for a sensitivity of 90 % and +/−35 % (26.4 %, 87.8 %) for a sensitivity of 60 %. The corresponding figures for specificity are +/− 5 % (84.8 %, 93.9 %) for 90 % specificity and +/− 7 % (52.7 %, 67.0 %) for 60 % specificity.

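### Objective 4 names only kappa, which cannot show whether thromboelastometry over-recommends or misses treatment relative to the reference tests

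*Protocol article*

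**What the plan says.** The Protocol article, Aims and objectives, sets the fourth objective as: "To investigate the agreement between the treatment recommended by the results of the reference tests and the treatment recommended by the TEM test results". Under Statistical analyses the method is: "The agreement between the recommended treatments resulting from the reference tests and the TEM test results will be assessed using Kappa statistics". No other statistic is attached to that objective.

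Aims and objectives also gives two ways in which the study might bring benefit. The first is that "test results may improve selection of the best treatments for children with blood clotting abnormalities to prevent or stop excessive bleeding". The second is that "test results may prevent the use of unnecessary treatments in children who do not have blood clotting abnormalities".

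For objective 3, Statistical analyses lists sensitivity, specificity, likelihood ratios and predictive values. These compare TEM with types of clotting abnormality defined by the reference tests, not with recommended treatments.

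Under Sample size calculation, "The study size is 200 participants with blood samples taken" and "we have considered two alternative estimates of prevalence of blood clotting abnormalities", namely 30% and 5%. That section gives no figure for objective 4 and no rate at which any treatment is expected to be recommended.

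**The concern.** When TEM and the reference tests disagree about a treatment, they can do so in two ways. TEM may recommend it when the reference tests do not (an over-recommendation relative to the reference), or the reference tests may recommend it when TEM does not (a miss). The first bears on the hoped-for avoidance of unnecessary treatment, the second on the hoped-for better selection of treatment. Kappa combines the two and does not change when they are exchanged.

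Kappa also depends on how often the treatment is recommended, even when the accuracy of TEM is held fixed. If kappas for several treatments are set side by side, a reader may take a difference in frequency for a difference in TEM performance.

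Objective 4 is the only objective framed in terms of treatment recommendations, and the abstract says the study will inform the design of randomised trials. A kappa reported without direction would not tell the designers of those trials which kind of error to expect.

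**Working it through.** **Inputs.** N = 200; prevalences of 30% and 5%; sensitivity and specificity of 90% or 60% (all from Sample size calculation). The article gives no recommendation rates, so I assume that a treatment is recommended exactly when the abnormality is present. The prevalences then stand in for reference recommendation rates.

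**The plan's own figures.** None is given for kappa. The tables behind the objective 1 and 3 precision statements can be checked with exact binomial intervals:
- 60/200 gives 23.7% to 36.9%, 54/60 gives 79.5% to 96.2%, and 126/140 gives 83.8% to 94.4%, all as stated.
- At 5% prevalence, 10/200 gives 2.4% to 9.0% and 171/190 gives 84.8% to 93.9%, as stated. 9/10 gives 55.5% to 99.7%, against a stated 55.5% to 100%, a trivial difference.

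The 2x2 tables below therefore use the plan's own planning counts.

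**Formula.** Let a = both recommend, b = TEM only, c = reference only, d = neither. Then po = (a + d)/N, pe = [(a + b)(a + c) + (c + d)(b + d)]/N², and kappa = (po − pe)/(1 − pe). Exchanging b and c leaves po and pe unchanged, so kappa is symmetric in the two errors whatever the data.

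**Direction, with 60 of 200 reference-positive.**

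| | a | b | c | d | po | pe | kappa |
|---|---|---|---|---|---|---|---|
| Over-recommendation only | 60 | 40 | 0 | 100 | 0.800 | 0.3×0.5 + 0.7×0.5 = 0.500 | 0.300/0.500 = 0.60 |
| Misses only | 31 | 0 | 29 | 140 | 0.855 | 0.3×0.155 + 0.7×0.845 = 0.638 | 0.217/0.362 = 0.60 |

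In the first row TEM misses none of the 60 and over-recommends in 40 of 140 (29%). In the second it misses 29 of 60 (48%) and over-recommends in none. Kappa is the same to two decimals.

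A direct exchange shows the symmetry exactly: the tables (60, 24, 0, 116) and (60, 0, 24, 116) both have po = 0.88, pe = 0.532 and kappa = 0.348/0.468 = 0.744.

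**Frequency, with sensitivity and specificity both 90%.**
- At 30% the table is (54, 14, 6, 126). po = 0.90, pe = 0.3×0.34 + 0.7×0.66 = 0.564, kappa = 0.336/0.436 = 0.77.
- At 5% the table is (9, 19, 1, 171). po = 0.90, pe = 0.05×0.14 + 0.95×0.86 = 0.824, kappa = 0.076/0.176 = 0.43.

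The same fall appears at the plan's other accuracy values (sensitivity/specificity, 30% then 5%): 60/90 gives 0.525 and 0.29; 90/60 gives 0.40 and 0.11; 60/60 gives 0.17 and 0.05.

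**What the fall means.** Positive agreement is 2a/(2a + b + c) and negative agreement is 2d/(2d + b + c).
- At 30%: 108/128 = 0.84 and 252/272 = 0.93.
- At 5%: 18/38 = 0.47 and 342/362 = 0.94.

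At 5%, TEM recommends treatment in 9 + 19 = 28 children, of whom 9 (32%) are reference-positive. The lower kappa therefore partly records a real lack of agreement on whom to treat.

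Positive and negative agreement are themselves symmetric in b and c. They separate agreement to treat from agreement not to treat. Only the two discordant proportions give the direction.

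**The case against.** The strongest reply is that kappa is a standard measure for an objective worded simply as agreement. It is computed from a cross-table, and a condensed article may leave the display of that table to the full protocol or analysis plan. This stands in part: a reader might infer that nothing but kappa will be reported, and the article does not say so. What can be said is that the article commits objective 4 to one kind of statistic and names no directional measure there, although it lists several for objective 3.

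A second reply is that the study already looks at direction. That is true for abnormality types under objective 3, so it would be wrong to infer that the study is blind to direction. It does not settle objective 4, because the article gives no mapping from abnormality to recommended treatment.

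Other stronger readings also fail:
- A reader might infer that each child must fall into one treatment category. The text uses the plural for kappa, which fits one yes/no kappa per treatment, so several recommendations in one child are no obstacle.
- A reader might infer that the plan expects recommendation rates of 30% and 5%. Those are alternative planning scenarios for abnormalities.
- A reader might infer that the drop from 0.77 to 0.43 is purely an artefact of rarity. It is not, as the 9 of 28 shows. The 90% raw agreement is the flattering figure here, since never recommending treatment would agree in 95%.
- A reader might infer that the study's aim turns on this distinction. The overall aim is prediction of excessive bleeding, and the two benefits are offered only as possibilities.

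**Conclusion.** The point holds as a limit on what objective 4 can conclude from the statistic it names. Kappa cannot distinguish over-recommendation from missed recommendation: about 0.60 arises with 40 of the first and none of the second, or with 29 of the second and none of the first. It also differs between treatments by frequency alone, from 0.77 to 0.43 at 90% sensitivity and specificity, so kappas for common and rare treatments should not be compared directly.

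The symmetry and the dependence on frequency are properties of kappa and need no assumption. The particular values rest on equating recommendation with abnormality and on the plan's illustrative accuracies, not on observed data. The article makes no false statement here. Objective 4 carries no sample-size claim, and the primary outcome is unaffected. This is a worthwhile improvement in the analysis of one objective, not a threat to the study.

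**What to change.** In the objective 4 sentence of Statistical analyses, state that for each recommended treatment separately the report will give:
- the 2x2 table of TEM recommendation by reference recommendation;
- the proportions TEM-yes/reference-no and TEM-no/reference-yes, each with a 95% confidence interval;
- positive and negative agreement;
- kappa with its confidence interval.

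Add that treatments will not be ranked by kappa. If the full protocol or analysis plan already provides for these tables, a reference to them is enough.

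The data are those kappa already requires. Sample size, blood sampling and clinical care do not change. The only cost is a longer table.
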